### Plans to give access to the full protocol, participant level-data and statistical code {31c}

Direct access will be granted to authorized representatives from the sponsor, host institution, and the regulatory authorities to permit trial-related monitoring, audits, and inspections. In accordance with our study protocol, access to study data by independent researchers will be considered following the completion of the trial and publication of primary results. Requests for data access will be subject to review by the Principal Investigator and study team to ensure compliance with ethical and regulatory requirements, protection of participant confidentiality, and preservation of intellectual property rights. Access to data will be granted upon approval of a data-sharing agreement outlining the terms and conditions of data use, including appropriate acknowledgments and restrictions. We are committed to promoting transparency and scientific collaboration while safeguarding the interests of study participants and stakeholders.

## Oversight and monitoring

### Composition of the coordinating center and trial steering committee {5d}

This is an investigator-initiated study. The PI and research team will collectively manage all aspects of the research process, including protocol development, participant recruitment, data collection, analysis, and reporting. Although there isn’t a designated management team or external steering committee, internal mechanisms have been established to ensure rigorous oversight and adherence to ethical, regulatory, and institutional guidelines.

### Composition of the data monitoring committee, its role and reporting structure {21a}

The study will be monitored by a local extern monitor independent from PI. The results of monitoring will be reported to the sponsor.

### Adverse event reporting and harms {22}

All AE’s occurring during the study observed by the investigator or reported by the participant, whether or not attributed to the device under investigation will be recorded on the eCRF as specified in the protocol. All Adverse device effects (ADE) will be recorded in the eCRF.

The following information will be recorded: description, date of onset and end date, severity, assessment of relatedness to device, other suspect drug or device, and action taken. Follow-up information should be provided as necessary.

The relationship of AEs to the device will be assessed by a medically qualified investigator or the sponsor/manufacturer and will be followed up until resolution or the event is considered stable.

All ADEs that result in a participant’s withdrawal from the study or are present at the end of the study, will be followed up until a satisfactory resolution occurs.

The Sahlgrenska University Hospital and the Department of Psychiatry for Affective Disorders will undertake an initial review of the information and ensure it is reported to the manufacturer. Events will be followed up until resolution, any appropriate further information will be sent by the research team in a timely manner.

Reporting to Läkemedelsverket will be done in liaison with the Chief Investigator and the Manufacturer.

In addition to the above reporting the Chief Investigator will submit once a year, throughout the trial, or on request a progress/safety report to Sahlgrenska University Hospital and Västra Götaland Region.

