In animal studies, the stimulation of the vagus nerve through iVNS has been shown to produce an immediate dose-dependent anxiolytic effect [55] and to enhance fear extinction and reduce anxiety in rat models of PTSD, after both, moderate [56, 57] and prolonged and repeated trauma [58]. In humans, taVNS has been shown to reduce anger outbursts in adults with Prader-Willi Syndrome [59], enhance recognition of emotions in healthy students [60], and improve depressive and anxiety symptoms in adults and adolescents with clinically-diagnosed depression albeit with uncertain evidence due to the scarcity of available controlled studies [41]. Moreover, 4 weeks of taVNS has been shown to increase amygdala functional connectivity in patients with depression in comparison with sham taVNS [61]. A single session of taVNS has been shown to acutely alter the recognition of briefly presented facial expressions of negative valence in adolescents with MDD and increase emotion recognition in controls [62], as well as boost mood after prolonged effort exertion in healthy participants [63], in comparison with sham taVNS. In sum, taVNS has been shown to be safe and well-tolerated in humans at the doses tested, with local skin irritation being the most common side effect, followed by headache and nasopharyngitis [64].

To our knowledge, the effect of taVNS on emotional vulnerability in individuals diagnosed with BPD has never been investigated.

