### Outcomes {12}

The primary outcome will be the change in negative emotional arousal from baseline, assessed immediately after the affect-induction procedure (post-induction ratings) using the PANAS. Negative emotional arousal will be measured through self-reported ratings of negative emotions on the PANAS (PANAS-N) at five time-points: baseline, after the neutral video, and after each of the three affect-inducing videos (designated as t1, t3, t4, t6, and t8 in Table 1). The means of the PANAS-N scores for each time point will be calculated and used to test the null hypothesis of no difference between the taVNS and sham taVNS groups. A mixed model analysis will be employed to assess each time point separately, ensuring comprehensive evaluation across all time points. The PANAS-N scores have already been used to measure the emotional arousal in previous studies using the same affect induction procedure with BPD patients and have been shown to be able to detect within and between groups differences [28]. The GSR recording, a physiological measure of emotional arousal, will be performed throughout the entire procedure and used to validate the PANAS-N data.

Since an increased emotional reactivity/intensity, one of the three components of the emotional vulnerability together with emotional sensitivity and longer emotional recovery time, is central in the physiopathology of BPD and the underpinning for many of the related symptoms and dysfunctional behaviors (e.g., self-harm) [5], to test the effect of taVNS on this primary outcome may have direct clinical utility. The available psychological treatments are associated with an improvement in the emotional regulation of BPD patients but have uncertain effects on the underlying emotional vulnerability [33].

The secondary outcomes of the study include:Change in negative emotional arousal from baseline at prior to affect induction (pre-induction ratings) as assessed by PANAS.Change in negative emotional arousal from immediately after affect-induction at 4 min after affect induction (recovery ratings) as assessed by PANASPerceived effectiveness in managing emotions (PEME) scores (0–9) during affect induction.

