#### Participation Quality Evaluation

After the completion of the stimulation procedure and assessment, the following additional questions will be administered to participant to evaluate the quality of their participation (Participation Quality Evaluation or PQE): *To what extent did you empathize with the characters in the film? (Repeated for all the four videos); Did you close your eyes during any of the videos in this part of the experiment? Did you feel extremely uncomfortable with regards to the content in the videos? Did you feel that you let yourself experience the emotions that you were experiencing? Was it difficult to do this because someone else was in the room with you? Had you seen any of the video clips used in this study before? How was your attention during the procedure? Was there anything distracting? Were there other barriers to your participation? Is there anything that could be improved or done to reduce your burden? Do you want to leave some other comments on something that you think is worthwhile or important?*

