### Plans to promote participant retention and complete follow-up {18b}

The study was designed to minimize as much as possible the burden for the participants. The entire procedure will be completed in a period of two hours during which the investigator will always be present in the room to assist the participant with all potential problems or difficulties experienced. In case of discontinuation of participation for any reason, the participant will be asked to complete the PQE (see above) to further assess the reasons for discontinuation if not directly expressed by the participant or evident to the investigator. A follow-up visit will be offered to the participant in case of discontinuation due to AE.

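### Adverse events are captured by an investigator who knows the arm, with no question on stimulation symptoms and no scheduled later contact for participants who complete the session

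*Protocol article*

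**What the plan says.** **How events are captured.** Adverse event reporting and harms {22} covers all events "occurring during the study observed by the investigator or reported by the participant", regardless of whether the device is thought to be the cause. Relatedness is judged by a medically qualified investigator or by the sponsor or manufacturer. ADEs that lead to withdrawal or are still present at the end of the study are followed until satisfactory resolution.

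**Who knows the arm.** Who will be blinded {17a} blinds participants alone. Electrode position differs visibly between the arms.

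**How long the participant is seen.** Plans to promote participant retention {18b} states: "The entire procedure will be completed in a period of two hours during which the investigator will always be present in the room".

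**Contact afterwards.** Sections {11b}, {30} and {18b} offer visits or calls when a participant is withdrawn or discontinues because of an adverse event. No other contact after the session is described.

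**What is asked at the end.** The Participation Quality Evaluation (PQE), answered in the Qualtrics survey, covers empathy with the characters, closing the eyes, attention, distraction, barriers, burden and free comments. Its item closest to a harm is "Did you feel extremely uncomfortable with regards to the content in the videos".

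**The concern.** The Discussion calls this the first evaluation of taVNS in BPD and supports adjunct use by pointing to its safety profile and few side effects. Readers will therefore look to this trial's harm record, even though efficacy is the aim.

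Two features weaken that record. First, no described instrument asks the blinded participant about symptoms of stimulation, so physical events must be noticed by, or mentioned to, someone who knows the allocation. Whether a mild headache or a reddened ear is written down can then depend on the arm. Second, a completer is not described as being contacted again, so a later event enters the data only if someone happens to report it. A record with few events could reflect the method of collection as much as tolerability.

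**Working it through.** The plan gives no figure for harm ascertainment, so there is none to reproduce. The check sets the sections side by side.

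1. **Route during the visit.** Section {22} gives two routes: investigator observation and participant report. With {17a}, the investigator at the end of both routes is unblinded. The PQE is a third channel that the investigator does not filter, but none of its listed items concerns the ear, headache or any other stimulation effect.

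2. **Route after the visit.**
   - Withdrawn or discontinued because of an AE: visits or calls ({11b}, {30}, {18b}).
   - Event already recorded, or ADE present at study end: followed up ({22}).
   - Completer whose event starts later: no scheduled contact in any section.

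3. **Timing.** From the point where the stimulation dose is set: 4 min + 4 × (4 + 4) min + 3 × 1.5 min = 40.5 min, consistent with a 45-minute session inside a two-hour visit. The last emotion rating closes 4 + 1.5 = 5.5 min after the last clip. That is an efficacy rating and does not mark the end of safety observation.

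4. **Named effects.** Background and rationale {6a} lists "local skin irritation being the most common side effect, followed by headache and nasopharyngitis". No onset times are given. Skin irritation and headache can appear during the visit, and a direct question would pick them up.

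5. **Linking a late report.** Data management {19} says that no key between ID number and name will be used. The article therefore describes no way to attach a later call to the right record and arm.

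6. **Size, by assumption.** Let p be the true event rate and c the fraction captured; neither is in the documents. The chance of recording at least one event in n = 21 is 1 − (1 − pc)^21. With p = 10%:
   - c = 1: 1 − 0.90^21 = 89%
   - c = 0.5: 1 − 0.95^21 = 66%
   - c = 0.1: 1 − 0.99^21 = 19%

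   With no event recorded and full capture, the one-sided 95% upper limit is 1 − 0.05^(1/21) = 13.3% per arm (6.9% for all 42). If only half are captured, the limit on the true rate becomes 13.3% / 0.5 = 26.6%. The 13.3% itself is a property of n = 21 and does not measure the defect. Only the loosening by 1/c does, and c is unknown.

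**The case against.** **The article defers to a fuller document.** Section {22} says events "will be recorded on the eCRF as specified in the protocol", and that protocol is not shown. It may define how events are elicited and when collection ends. This stands: it cannot be claimed that observation and report are the only routes. But the article is not silent on follow-up. Three sections describe it, each time for AE-related withdrawal or discontinuation.

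**A reader might infer that the plan cannot detect delayed risks that it names itself.** The documents do not support this. No risk is called delayed. That nasopharyngitis comes late is an inference, because no onset time is given. Self-harm and slow return to emotional baseline are presented as features of BPD, not as hazards of the procedure. A reader might also equate the AE period with two hours, but that is the length of the procedure. The words during the study have no stated end, a participant may report later, and some have ongoing contact with the department.

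**The filter is partial.** Events are recorded whether or not attributed to the device, relatedness may be judged by the sponsor or manufacturer, and the PQE invites free comments. This stands as mitigation. It does not replace a direct question, because an event must be noticed or mentioned before these rules apply.

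**No objective or outcome compares harms between arms.** Correct, and with 21 per arm such a comparison is descriptive. This lowers the stakes but does not remove the value of collecting harms in the same way in both arms.

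**Later contact costs more than it seems.** This stands too. There is no ID-name key and recruitment began in March 2023, so follow-up would differ before and after the change.

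**Conclusion.** The point holds in a limited form. As the article describes it, harms are ascertained through an unblinded investigator around one two-hour visit, the end-of-session questionnaire does not ask about stimulation effects, and an event first appearing after a completer leaves has no scheduled route into the data. Under-ascertainment and filtering by arm are possible; neither is shown to occur, and their size cannot be derived from the documents. The percentages under working rest on assumed rates and capture fractions.

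The conclusion assumes that the full protocol and the schedule table, neither shown, add no structured symptom question or completer contact. If they do, a sentence in the article settles the matter. Nothing in section {22} is contradictory, and the efficacy analysis is unaffected. This is an inexpensive improvement to the harm record, not a flaw that undermines the trial.

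**What to change.** - Add to the existing end-of-session Qualtrics survey a short self-completed symptom list, identical in both arms: skin irritation at the ear, headache, any other symptom, and current distress compared with arrival.
- State in section {22} when the AE window closes.
- Report solicited and volunteered events separately by arm.
- Optional, if the sponsor judges it feasible: repeat the list once for remaining participants, at one fixed interval chosen by the sponsor, through a survey link that carries the study ID. The link should be handed over at the visit, because {19} keeps no ID-name key.

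The cost is a few survey items and an amendment. More minor events will be recorded, and participants already enrolled will lack the list, so the report should say from which participant onward it was used. The optional repeat adds at most 42 brief survey contacts, fewer now that recruitment is under way.

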### Frequency and plans for auditing trial conduct {23}

In accordance with the nature of this investigator-initiated study, the roles and responsibilities of the coordinating center and trial steering committee are fulfilled by the PI and the research team. The PI assumes leadership in all aspects of the study, overseeing protocol development, participant recruitment, data collection, analysis, and reporting. Internal mechanisms have been established to ensure thorough oversight and adherence to ethical, regulatory, and institutional guidelines. Regular team meetings and protocol reviews facilitate continuous monitoring of study progress and prompt action to address any issues or challenges encountered during the research process.

### Plans for communicating important protocol amendments to relevant parties (e.g., trial participants, ethical committees) {25}

The protocol, informed consent form, participant information sheet, and any proposed advertising material have been submitted to the appropriate Research Ethics Committee (Etikprövningsmyndighet), regulatory authorities (Läkemedelsverket), and host institution (Sahlgrenska University Hospital) for written approval. The Investigator will submit and, where necessary, obtain approval from the above parties for all substantial amendments to the original approved documents.

### Dissemination plans {31a}

All results will be published in peer-reviewed scientific journals and all contributing authors will be included in accordance with the Vancouver recommendations.

## Discussion

We have described our protocol for a randomized controlled trial to evaluate the efficacy of one taVNS session to acutely decrease emotional vulnerability and improve emotional regulation in patients with BPD.

To the best of our knowledge, this study represents the initial exploration into the acute effects of taVNS on the three facets of emotional vulnerability outlined in Linehan’s biosocial model [5] among individuals diagnosed with BPD. Furthermore, this investigation marks the first instance of evaluating taVNS in this population. We believe that our study will help to better understand the involvement of vagal tone in emotional vulnerability and regulation in BPD patients and possibly lead to the development of new treatment strategies.

TaVNS offers a non-invasive, portable, and user-friendly option, allowing for convenient “as needed” use. Notably, emotion dysregulation, stemming from emotional vulnerability, is a central feature of many serious BPD-related challenges, such as self-injury and impulsive behaviors. Addressing emotional vulnerability is a key aspect of Dialectical Behavioral Therapy (DBT) [5], one of the few therapies showing efficacy for the treatment of BPD [77]. Current approaches often involve off-label use of medications with significant side effects, as there are limited interventions available [78]. Given its safety profile and minimal side effects, taVNS could serve as a valuable adjunct to psychotherapy or medication, enhancing treatment options for individuals with BPD. If taVNS will be shown to be efficacious to acutely decrease emotional vulnerability and improve emotion regulation, future research should explore the potential of using taVNS alongside standard BPD treatments in real settings. Potential future studies could investigate the impact of an as-needed use of taVNS in adjunct to psychotherapy, on the frequency or severity of dysfunctional self-regulating behaviors like, for example, self-harm or drug abuse, in comparison with psychotherapy alone. Additionally, given that the present study will not give information on the long-lasting effects of taVNS, or on the effects of a prolonged taVNS use, on emotional vulnerability and regulation, it would be worthy to investigate the efficacy of a daily taVNS treatment, on these two dimensions and the related BPD symptoms. Finally, in case of acute efficacy of taVNS on emotional vulnerability and/or emotional regulation, there could be a potential for its application in the treatment of other psychiatric disorders characterized by emotional dysregulation and autonomic imbalance, as PTSD or complex-PTSD.

## Trial status

tVNS-BPD-001, 10/OCT/2022 v.1.0. The recruitment began the 24/MAR/2023 and is expected to be completed the 31/SEP/2025

## Data Availability

Direct access will be granted to authorized representatives from the sponsor, host institution, and the regulatory authorities to permit trial-related monitoring, audits, and inspections.

## Abbreviations

ACC: Anterior cingulate cortex
ADE: Adverse device effect
AE: Adverse event
BPD: Borderline personality disorder
BSL-23: Borderline Symptom List 23
BSL-SUPP: Borderline symptom list - behavior supplement
CAN: Central autonomic network
DERS: Difficulties in Emotion Regulation Scale
dlPFC: Dorsolateral prefrontal cortex
ECG: Electrocardiogram
eCRF: Electronic case report form
EMA: European Medicines Agency
FDA: Food and Drug Administration
GABA: Gamma-aminobutyric acid
GSR: Galvanic skin response
HRV: Heart rate variability
iVNS: Invasive vagus nerve stimulation
MDD: Major depressive disorder
MINI: The Mini International Neuropsychiatric Interview
mPFC: Medial prefrontal cortex
NIM: Neurovisceral integration model
NTS: Nucleus tractus solitarii
PANAS: Positive and Negative Affect Schedule
paVNS: Percutaneous auricular vagus nerve stimulation
PEME: Perceived effectiveness in managing emotions
PI: Principal Investigator
PQE: Participation Quality Evaluation
PVT: Polyvagal theory
rACC: Rostral anterior cingulate cortex
SCID-5-PD: Structured Clinical Interview for DSM-5 Personality Disorders
sgACC: Subgenual anterior cingulate cortex
SIL: Subject Information Leaflet (see PIL)
taVNS: Transcutaneous auricular vagus nerve stimulation
tcVNS: Transcutaneous cervical vagus nerve stimulation
tVNS: Transcutaneous vagus nerve stimulation
VNS: Vagus nerve stimulation
